### Research hypotheses

The research hypotheses of this proposed study include the following:

The intervention group would show a significant reduction in depression, anxiety, and stress than the control group right after intervention and during follow-up.The intervention group would significantly increase life satisfaction and empowerment more than the control group right after intervention and during follow-up.The intensity and frequency of mindfulness practice would moderate the relationship between participants’ cognitive appraisal of daily life events and psychological distress and mental well-being in the intervention group.

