#### Sample size

The sample size calculation for this study is based on the linear mixed model that will be adopted to answer research questions 1 and 2 based on the repeated ecological momentary assessment data from the intervention and control group and the effect size of 0.29 from previous studies (unpublished manuscript). The R package *sjstas* [44], and *pwr* [45] were used for sample size calculation. The results indicate that a total of 536 participants will be required to detect a significant difference at an alpha level of 0.05 and a power of 80%. Accounting for potential dropouts, we conservatively estimate that 20% of participants may not complete the study. Therefore, we plan to recruit 670 participants (335 in each group).

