**Fig 3 pone.0291168.g003:**
[figure not shown]
Summarizations of measurements.

*The cognitive Appraisal of Health Scale* will be used to measure participants’ cognitive appraisal of daily life events. This scale includes 28 items rated from 1 strongly disagree to 5 strongly agree. This scale was developed based on the transactional theory of stress and coping and thus consists of subscales of primary appraisal (threat, challenge, harm/loss, and benign/irrelevant) and secondary appraisal. The internal consistencies were all greater than 0.70 [46].

*The Five Facet Mindfulness Questionnaire (FFMQ)-short version* [47, 48] will be used to measure participants’ level of mindfulness before and after practicing. It includes 15 items measuring the five facets of mindfulness: observing, describing, acting with awareness, non-judging of inner experience, and non-reactivity to inner experience. This scale was further validated [49] and yielded good convergent validity and internal consistency [49].

Parents’ psychological distress will be assessed in the domains of depression, anxiety, stress, and mental well-being, indicating participants’ life satisfaction and empowerment.

*The Depression Anxiety Stress Scale (DASS)* [50] is a self-report questionnaire that measures the emotional states of depression, anxiety, and stress. This scale contains 21 questions rated from 0 (did not apply to me at all) to 3 (applied to me very much, or most of the time). There were seven questions for each sub-scale of stress, depression, and anxiety [51]. This scale was reliable (alpha = 0.96 and 0.80 for the depression and anxiety subscales, respectively). Cronbach’s alpha was high for the three subscales in parents of children with ASD: 0.91 for stress, 0.87 for anxiety, 0.94 for depression, and 0.92 for full scale [51]. It has also been validated in the Hong Kong population [52].

*Satisfaction with Life Scale (SWLS)* [53]. The SWLS has five items scored on a 7-point scale (1 = strongly disagree to 7 = strongly agree) measuring participants’ satisfaction with life and has a Cronbach’s alpha for internal consistency of 0.87 and a test-retest correlation of 0.82 [53]. This scale has also been validated in Chinese [54] and Hong Kong populations [55].

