### Data analysis

Data analysis will be conducted using STATA 17 [60]. All significance tests were two-sided with a 5% level of significance. Missing data will be calculated using intention-to-treat approach. Participants who failed to answer the prompted questions will be treat as no improvement on the outcomes. The characteristics of the observed data and the missing data will be compared to determine whether there are any systematic differences. If tested that the missing data will be missing not at random, imputation methods, such as multiple imputation (MI) or maximum likelihood estimation (MLE), will be adopted to estimate the missing values based on the observed data and the relationships between variables. Moreover, sensitivity analysis will be adopted to assess the impact of the missing data on the study results and to determine the robustness of the findings. Complete case analysis and multiple imputation will also be conducted as sensitivity analysis. The internal consistency of the constructs for mindfulness, depression, anxiety, stress, and life satisfaction will be assessed with Cronbach’s alpha. In each construct, the PI will sum all items to build the score for that attribute in each participant.

To answer the first and second questions, first of all, the effect size (Heges’ g) of the outcome for both the intervention and control groups will be calculated. Subgroup analysis will be conducted when necessary. Next, linear mixed models will be conducted to compare the effectiveness of the mindfulness intervention between the two treatment groups. Linear mixed models are particularly suitable for analyzing data collected via ecological momentary assessment, as they can account for the nested and repeated nature of the data. The main predictor variable will be the treatment group (intervention vs. control), and the model will also include baseline DASS scores and any relevant demographic variables (e.g., age, gender) as covariates. The linear mixed model will include random intercepts and slopes for each participant to account for individual differences in the baseline scores and the rate of change in scores over time. The treatment group effect will be assessed using a fixed effect, and the model will also include an interaction term between treatment group and time to investigate any differential effects of the intervention over time.

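### The between-arm mixed model is justified by EMA data that only the intervention arm is described as giving; on the three shared surveys its random-effects structure fits poorly, and its group coefficient reads as a difference at baseline

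*Protocol article*

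**What the plan says.** **Model.** Under Data analysis, one linear mixed model answers the first and second research questions. On random effects: "The linear mixed model will include random intercepts and slopes for each participant to account for individual differences in the baseline scores", with the slopes described as a rate of change in scores over time. On covariates: "the model will also include baseline DASS scores and any relevant demographic variables". On the estimand: "The treatment group effect will be assessed using a fixed effect". A group-by-time interaction is added to look for differential effects over time. The section recommends this model because it suits EMA data.

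**Data.** Sample size says the model rests on repeated EMA data from both arms. The Abstract has the intervention group install the app, and Trial design lists EMA among the components that group receives. Controls are described as getting the same longitudinal survey plus mindfulness messages. Outcomes has the questionnaires administered to both groups at baseline, post-test and follow-up. It places the daily short-form distress scale inside the app.

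**Hypothesis 1.** "The intervention group would show a significant reduction in depression, anxiety, and stress than the control group right after intervention and during follow-up".

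**The concern.** Random slopes are easy to support with many daily ratings per person. They are hard to support with two or three surveys, which is all the document describes for the control arm. The document is therefore inconsistent about the data behind its main comparison, and the model was chosen for the richer version.

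Once an interaction with time is in the model, the group coefficient is the arm difference at time zero. The plan ties the random intercepts to baseline scores. A random intercept is a person's deviation at time zero, so time zero reads as baseline, where randomisation makes the expected difference nil. The coefficient named as the treatment effect would then not be the effect at 8 weeks or at follow-up, the two times in Hypothesis 1. An effective intervention could be reported as null, or the model could be changed after the data are seen.

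The same model serves the second question. Read literally, SWLS and PES are adjusted for baseline DASS and not for their own baselines, although those are collected.

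**Working it through.** **Inputs.** From the document: "All significance tests were two-sided with a 5% level of significance"; "a total of 536 participants will be required to detect a significant difference at an alpha level of 0.05 and a power of 80"%; "the effect size of 0.29 from previous studies (unpublished manuscript"). Completers per arm: 536 / 2 = 268. The surveys fall at about months 0, 2 and 4.

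Assumed here: 0.29 is a standardised difference; SD 1 at each survey; equal correlation ρ = 0.5 between surveys (range 0.3 to 0.7); a true effect of 0.29 SD at both later surveys unless stated. Effects are given in absolute size.

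**The plan's own figure.** 536 / 0.80 = 670 reproduces. A plain two-group comparison at 0.29 needs 2 × (1.96 + 0.84)² / 0.29² ≈ 187 per arm, 374 in total, so 536 does not reproduce from the stated inputs. That is a separate matter; 268 per arm is used here only as the trial's size.

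**Step 1: identification.** Let a, b and c be the intercept variance, slope variance and their covariance, and e the residual variance. With responses at months 2 and 4 only:
- Var(month 2) = a + 4c + 4b + e
- Var(month 4) = a + 8c + 16b + e
- Cov = a + 6c + 8b

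This gives three moments for four unknowns (Jacobian rank 3), so the components are not identified. With c = 0 there are three unknowns and rank 3: just identified. With baseline as a third response there are six moments for four unknowns (rank 4): identified, but baseline is then outcome and covariate at once. In 20 simulated fits of that version, 55% converged. The fixed effects (intercept, group, time, group-by-time, baseline) have full rank, 5 of 5, with two post-baseline surveys.

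**Step 2: the group coefficient if baseline is a response, with linear time from baseline.** The least-squares line through effects (0, 0.29, 0.29) has mean 0.58 / 3 = 0.193 and slope 0.29 / 2 = 0.145 per survey.
- At baseline: 0.193 − 0.145 = 0.048. This is the group coefficient.
- At 8 weeks: 0.193.
- At follow-up: 0.193 + 0.145 = 0.338.

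The simulation for the table below left baseline out as a covariate. In the 20 fits that had it as both, the group coefficient averaged 0.056.

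**Step 3: the group coefficient if baseline is only a covariate, with time still counted from baseline.** The line passes through both later surveys, so its value at month 0 is 2 × (8-week effect) − (follow-up effect).
- Effects 0.29 and 0.29: 0.29
- Effects 0.29 and 0.15: 0.43
- Effects 0.145 and 0.29: 0

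Precision: at ρ = 0.5, adjustment for baseline leaves variance 1 − 0.25 = 0.75 and covariance 0.5 − 0.25 = 0.25.
- Extrapolation: (5 × 0.75 − 4 × 0.25) × 2/268 = 0.0205, SE 0.143, z = 0.29 / 0.143 ≈ 2.02, power about 52%.
- 8-week contrast: 0.75 × 2/268 = 0.0056, SE 0.075, z ≈ 3.88, power about 97%.

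**Step 4: simulation, 268 per arm, 400 runs, effect 0.29 at both later surveys.**

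| Reading | Mean group coefficient | Rejection at ρ = 0.5 (range over ρ = 0.3 to 0.7) |
|---|---|---|
| Baseline a response, time 0 = baseline | 0.05 | 10% (9–11%) |
| Baseline a covariate, time 0 = baseline | 0.29 | 52% (41–70%) |
| Baseline a covariate, time 0 = post-test | 0.29 | 97% (95–99.5%) |

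Under the first reading the group-by-time term rejects in 92% of runs (79–99.5%). The signal is present, but not in the coefficient the plan names.

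**Step 5: two side figures.** Three subscales at two times is six tests; 1 − 0.95⁶ = 0.26. For SWLS, with "a test-retest correlation of 0.82", 1 − 0.82² = 0.33 and √0.33 = 0.57, an SE 43% smaller than with no adjustment. Neither is an expected loss (see the verdict).

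**The case against.** The strongest reply is that the plan is under-specified rather than wrong. It does not state the time origin, whether time is linear or categorical, the covariance of the random effects, or whether baseline is a response. Such details often sit in an analysis plan, and neither that nor the approved protocol is shown. With time zero at post-test, the group coefficient is the 8-week effect. Non-identification needs two responses and a free intercept-slope covariance. The two difficulties also rest partly on different readings: keeping baseline as a response cures identification, and in the equal-effects case the covariate-only reading gives 0.29, not 0.05. If controls did supply daily EMA, as Sample size says, random slopes would be supportable.

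Much of this stands. A reader might infer that the model cannot be estimated, or that the primary test is simply wrong; the document supports neither. The fixed effects are estimable throughout, independent random effects are just identified, and failure to converge is a risk, not a certainty.

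What the reply does not remove is the wording the plan does contain. Linking intercepts to baseline scores and slopes to a rate of change points to time counted from baseline, which sits badly with the post-test origin that would rescue the group term. Nor does it remove the conflict over EMA in the control arm, which lies within this one document.

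**Conclusion.** The point holds in limited form. On the three surveys that both arms are described as completing, the stated model is poorly matched to the data. On the most natural reading, the coefficient named as the treatment effect is either the arm difference at baseline (about 0.05 SD for a true 0.29 SD at both later surveys) or an extrapolation to baseline with about 52% power, where the 8-week contrast would have 97%. These figures rest on 268 per arm, equal correlations of 0.5 and a constant effect; the ranges are in the table. They do not apply if time zero is set at post-test.

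Two stronger inferences should be resisted. The 26% family-wise figure assumes six independent tests; subscales of one questionnaire measured twice in the same people are correlated, so it is an upper value. The 43% gain for SWLS compares with no adjustment rather than with the planned covariates, and assumes that a published test-retest correlation of 0.82 holds over the trial interval. What remains is that adjusting SWLS and PES for their own baselines costs nothing and should be stated.

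**What to change.** For the between-arm comparison, take the 8-week and follow-up surveys as the responses. Include arm, visit as a category, arm-by-visit, the baseline value of the same outcome (DASS for DASS, SWLS for SWLS, PES for PES) and baseline-by-visit, with an unstructured within-person covariance and no random slopes. The 2 × 2 covariance has three parameters for three moments, and no time origin or straight line is involved.

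Report the arm difference at each visit from this model, and state in advance which one is the primary contrast. Hypothesis 1 covers both times, so that choice is the sponsor's.

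Reconcile Sample size and Data analysis with the Abstract and Trial design on whether controls provide EMA. If they do not, confine EMA-based mixed models to analyses within the intervention arm.

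The cost is wording only, with no change to data collection, and it should be settled before outcome data are seen. Naming one primary contrast means that the other time point loses primary status.

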### Oversight and monitoring

#### Composition of the data monitoring committee, its role, and reporting structure

A project team will be formed, including all investigators of Lingnan University, HKU, and the agencies where the investigators recruited the participants. The team will meet regularly to design the project’s training, intervention, and operation. The authors from the agencies will provide more expert advice on frontline counseling and recruitment, while HKU will provide more consultation on the evaluation and result dissemination.

#### Strategies for improving adherence

After everyday mindfulness practice, participants will be reminded to take the daily mental status assessment via EMA. The measurements will be collected and checked by research assistants via the Dashboard, allowing the RA to track each participant’s adherence. For those participants who failed to complete the assessment and practice mindfulness, the RA will send a reminder through WhatsApp.

#### Adverse event reporting and harms

The proposed mindfulness-based intervention is a behavioural approach without invasive procedures and medication; no side effects or adverse outcomes will be expected. All participants will be asked at telephone follow-up by the research assistant if they encounter difficulties using the smartphone app. If so, and the participant agrees, the research assistant will refer these participants to the specialists.

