#### Intervention description

*EMI/A-MBI app*. The EMI/A-MBI app will include five main parts: a virtual counselor (a chatbot with pre-set algorism for responding to participants), an intervention library, weekly mindfulness practice, an assessment bank, and a daily emotion log. In the eight weeks, the virtual counselor in the chatbot will initiate the conversation every day three times (morning, afternoon, and evening) to check the status of the participants. If the participants responded, the virtual counselor would invite them to rate their depression, stress, and anxiety and then recommend appropriate mindfulness practices in the intervention library, such as 3-minute breathing space or mindful eating. The conversation between the virtual counselor and participants will be in the format of a menu list, and participants can easily choose from different options. After the participants finish the mindfulness practice, the virtual counselor will check the participants’ mental health status again. Suppose the participants do not respond to the virtual counselor for the whole day. In that case, the EMI/A-MBI app will prompt a short survey for psychological distress from the assessment bank and recommend mindfulness practice at the end of the day. Participants can also initiate the conversation with the virtual counselor at any time of the day, and the process will be the same. The participants can also go to the intervention library to find the mindfulness practice they prefer. The intervention library will include audio and videos of different mindfulness exercises, such as mindful walking, mindful yoga, or loving and kindness mindfulness. (Example description of the mindfulness practice can be found in S1 Table). Scripts of the audio and videos will also be provided in the intervention library. The daily emotion log will be prompted to the participants every morning since the second day of the intervention as a visual aid for participants to be aware of the change in their psychological distress and mental well-being. Every Saturday, the app will prompt reminders for the participants to join the formal 2.5-hour mindfulness practice. (The App design can be found in S2 File).

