#### The explanation for the choice of comparators

As mindfulness-based intervention has been proven effective for parents of children with autism, we will involve the components of mindfulness in both the intervention and control groups. Therefore, any extra effects incurred in the intervention group can be attributed to the benefits of using EMI and EMA.

The intervention will be discontinued or modified when participants report feeling more psychological distress while practicing mindfulness-based intervention.

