#### Outcomes

At baseline, post-test, and follow-up survey, the questionnaire contains the same questions concerning demographic information (will only ask at baseline). Psychological distress and mental well-being will be administered to participants in both intervention and control groups. Demographic information, including parent and children’s gender, parent and children’s age, years of children diagnosed with ASD, number of children living in the same household, family monthly income, parents’ education level, parents’ employment status, and average time spent with children daily. The primary outcome will be participants’ psychological distress measured by the depression anxiety stress scale. The secondary outcomes will include participants’ subjective well-being, measured by the satisfaction with life scale, and level of resilience, measured by the psychological empowerment scale. (Detailed measurement information can be found in Fig 3)

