#### Follow-up and incentive

To minimize the survey effect of EMI on the study outcomes and to assess the long-term impact of EMI/A-MBI, a telephone follow-up to assess the study outcomes will be conducted two months after the completion of the EMI/A-MBI.

The EMI validity largely relies on the participants’ compliance. Therefore, an attractive incentive is needed. All participants will be given a HK$50 gift voucher upon completing the baseline, post-study, and 2-month follow-up surveys. In addition, participants in the EMI group who have successfully completed all EMIs in the 8-week will be given an additional HK$50 gift voucher.

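### The plan foresees worsening distress during practice, but its harms section expects none, so individual deterioration and distress-related discontinuations are not counted by arm

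*Protocol article*

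**What the plan says.** Two sections of the protocol article deal with participants getting worse, and they do not refer to each other.

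- The explanation for the choice of comparators: "The intervention will be discontinued or modified when participants report feeling more psychological distress while practicing mindfulness-based intervention".
- Adverse event reporting and harms: because the approach is behavioural, with no invasive procedure or medication, "no side effects or adverse outcomes will be expected". The only enquiry planned there is this: "All participants will be asked at telephone follow-up by the research assistant if they encounter difficulties using the smartphone app". That section mentions neither distress nor the discontinuations that the comparator section provides for.

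The timing comes from Follow-up and incentive: "a telephone follow-up to assess the study outcomes will be conducted two months after the completion of the EMI/A-MBI".

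Distress itself is measured. Under Outcomes, the primary outcome is "psychological distress measured by the depression anxiety stress scale", and for the baseline, post-test and follow-up surveys "Psychological distress and mental well-being will be administered to participants in both intervention and control groups". In the app, the virtual counsellor "would invite them to rate their depression, stress, and anxiety" and then recommends a practice (Intervention description). Data analysis plans Hedges' g and linear mixed models with two-sided tests at 5%, and treats people who do not answer prompted questions as not improved.

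**The concern.** A plan that makes increased distress a reason to stop or change the intervention has recognised it as an unwanted outcome. The harms section then rules it out as an expectation, on grounds (no procedure, no drug) that do not bear on psychological worsening, and asks about something else. Followed as written, the plan produces no count of deteriorated parents and no count of distress-related discontinuations in either arm.

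This matters because the Discussion foresees policy use if the trial is positive, including insurance coverage and public programmes. A case of that kind needs benefit and harm side by side, by arm. A favourable mean on the DASS does not show that few parents got worse.

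**Working it through.** **1. Where worsening could be picked up.** These are the sections of the article that handle distress data, and the use each makes of them.

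| Section | What is collected or done | Stated use |
|---|---|---|
| Choice of comparators | Reports of more distress during practice | Discontinue or modify; no count or report planned |
| Adverse event reporting and harms | App difficulties, at the telephone follow-up | Referral to specialists |
| Outcomes | DASS, both arms, three time points | Primary efficacy outcome |
| Intervention description | Distress ratings in the app | Choice of practice |
| Strategies for improving adherence | Dashboard data checked by assistants | Adherence tracking and reminders |
| Data analysis | Hedges' g, linear mixed models | Average effect by arm |

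None of them defines individual worsening as a harm or says it will be counted.

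**2. What an average can hide.** Assume individual change is normal with SD 1 (not given in the article) and take a mean improvement of 0.29 SD, the effect size under Sample size. The share worsening by more than 0.5 SD is 1 − Φ(0.5 + 0.29) = 1 − Φ(0.79) = 0.215, about 21%. With no mean change it is 1 − Φ(0.5) = 0.309, about 31%. A pure mean shift therefore lowers the deteriorated share. For an improved mean to go with a higher share than 31%, the app arm needs more spread: 0.79/s < 0.5, so s > 1.58, against 1 in the comparison arm.

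**3. An example threshold.** Outcomes gives a full-scale alpha of 0.92. If alpha is taken as the reliability, the reliable-change cut-off is 1.96 × √2 × √(1 − 0.92) = 0.784 baseline SD. Alpha is internal consistency, not stability over 8 weeks or 2 months. With a reliability of 0.80 (the lowest DASS alpha quoted, used only to show the range), the cut-off is 1.96 × √2 × √0.20 = 1.24 SD.

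**4. Precision of a by-arm comparison.** Completers per arm: 536/2 = 268. With an assumed rate q in both arms, the half-width is 1.96 × √(2q(1 − q)/268).

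- q = 5%: 0.037, or 3.7 percentage points (13.4 completers per arm).
- q = 10%: 0.051, or 5.1 percentage points (26.8 completers per arm).

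**5. Effect of missing participants.** The planned 20% dropout is 335 × 0.20 = 67 per arm. If 10% of completers worsen and the missing are set to no improvement, and so counted as not worse, the rate is 26.8/335 = 8%. If all the missing were worse, it is (26.8 + 67)/335 = 28%. At 5% the two figures are 13.4/335 = 4% and (13.4 + 67)/335 = 24%. The handling of non-response can therefore move the result by more than the sampling error does.

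**The case against.** The strongest reply has four parts.

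- **A reader might infer that the trial will report no harms whatever its DASS data show.** The article does not support this. The DASS is the primary outcome and is compared between arms with two-sided tests, so an average worsening in the app arm would appear in the main result. Nothing forbids reporting harms.
- **A reader might also infer that harm is held to be impossible, or that distress is formally named as a risk.** Neither is in the text. The harms section states an expectation. The comparator section gives a trigger for action, which shows that some provision for worsening exists.
- **A deterioration analysis is commonly left to an analysis plan or full protocol, and neither is shown.** That is fair for the choice of threshold and model. It does not remove the conflict between two published sections, one of which is the article's dedicated harms section and makes a positive statement.
- **The proposed count has weaknesses.** The rates of 5% and 10% are assumptions, and the cut-off depends on the reliability used. The no-improvement rule would class parents who leave in distress as not worse. Reports that lead to discontinuation are also likely to be captured unevenly: the virtual counsellor contacts the app arm three times a day, while The control condition describes only audio practice reminders. (Sample size refers to momentary data from both groups, so this too needs to be made clear.) All of this stands, and the fix has to deal with it.

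**Conclusion.** The concern holds in a limited form. The two sections conflict. Because the harms section asks only about app difficulties, individual deterioration and distress-related discontinuations would go uncounted by arm, although the DASS data needed for the first are already collected in both arms at all three time points. Mean worsening would still be visible.

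The article gives no deterioration rate, so the size can only be illustrated. At assumed rates of 5% to 10%, about 17 to 34 of the 335 parents randomised to each arm would be affected (16.75 and 33.5). The claim that a favourable mean can coexist with many worsened parents rests on the normal-change assumption. An excess of worsened parents in the app arm despite a better mean would also need wider spread or skew in that arm; it is possible but not predicted by anything in the article.

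**What to change.** 1. Remove the statement that no side effects or adverse outcomes are expected, and reconcile the harms section with the comparator section so that both treat worsening distress in the same way. The clinical response to it is for the investigators and is not at issue here.
2. Prespecify a harm summary on the existing DASS data: the proportion in each arm worsening from baseline beyond a stated threshold, at 8 weeks and at 2 months, with a risk difference and 95% confidence interval. A reliable-change cut-off (about 0.78 baseline SD under the alpha of 0.92) is one example; the investigators choose.
3. Exempt this outcome from the no-improvement rule. Report the number missing by arm, with a sensitivity analysis.
4. Report discontinuations and modifications for distress by arm, descriptively, with a note that the app arm is prompted about distress daily and the control arm, as described, is not.

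Cost: one added analysis, a simple log for item 4, short text changes in the harms and analysis sections, and no new assessments. The downside is modest precision, about 4 to 5 percentage points either side at the assumed rates, for a result that must be reported even if unfavourable.
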